#### Patient diary

The patient diary is checked by the examiner during each study visit and reviewed and discussed with the patients. The patient diary is handed out to every patient during the first post-operative days at the first study visit. Patients are required to record the following variables: spasms by spasticity rating according to Penn Spasm Frequency Scale, medication (drug name and dosage), and any important subjective or objective changes in the neurological symptoms. The item spasms shall be documented on a weekly basis immediately after receiving the patient diary. Changes in medication or important events shall be documented depending on their occurrence after discharge from the hospital. All entries shall be dated.

#### Blood samples

Blood sample collection is optional at the baseline examination. If a blood sample has been taken at baseline, it is mandatory at every other follow-up visit. If no blood sample has been collected at baseline, no further blood samples are intended.

The blood tube (one 8-ml serum tube) is cooled after removal at 4 °C and then centrifuged at 3500*g* for about 15 min and then frozen to −80 °C. Parameters to be analyzed are pro-inflammatory and anti-inflammatory cytokines and proteins (some examples are S100b, IL-6, GFAP, NSE, tau, and pNF-H) and serological biomarkers which are discovered and published during the time course of the study.

Blood sample collection will only take place in those hospitals where technical feasibility is given (−80° freezer and a centrifuge).

Additionally, parameters from routine blood chemistry shall be documented in the eCRF at baseline, the 1st, 2nd, and 3rd follow-up exam. The following markers will be included in the eCRF: WBC, lymphocytes, eosinophils, PLT, MCHC, MCH, MCV, albumin, ALP, creatinine, bilirubin, uric acid, calcium, chloride, CO_2_ content, and sodium.

#### AIS/ISNCSCI

The neurological level of injury and injury completeness will be assessed according to the American Spinal Injury Association (ASIA) International Standards for Neurological Classification of SCI (ISNCSCI). The classification system contains three elements: ASIA Impairment Scale (AIS A–E), motor score (based on the neurological examination of muscle function), and sensory score (based on the neurological examination of sensory function) [5, 40–43].

#### Spasticity assessment

The degree of spasticity will be assessed with the self-rated Penn Spasm Frequency Scale (PSFS) [44–46] on a weekly basis in the patient diary.

We refrained from a clinically rated assessment of spasticity because the level of spasticity is known to vary over time; thus, a single clinical assessment will not necessarily reflect accurately an individual’s overall level of spasticity. The principal clinical outcome measure for spasticity has been the long-established Modified Ashworth Scale (MAS) [47, 48]. Previous literature investigating the MAS reported poor inter-rater reliability [49–52] and a poor correlation with self-rated assessments of spasticity [53]. Joint contractions further decrease the reliability of the MAS [52]. Furthermore, the MAS does not account for the dependence of the resistance to the velocity of the movement and therefore does not comply with the concept of spasticity [54].

#### Gait analysis

The following scores/gait tests are assessed in patients who regain walking ability with or without auxiliaries:
WISCI II (Walking Index for Spinal Cord Injury II)TUG (Timed Up and Go Test)10-m timed walk6-min walk test

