#### Secondary objective

The secondary objectives include the assessment of changes in spasticity, the ability to walk, urological function, quality of life, and independence in everyday life over time and in comparison between the groups.

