#### Secondary (exploratory) endpoints and control variables

AIS classificationDegree of spasticity according to Penn Spasm Frequency ScaleWalking abilityWISCI II (Walking Index for Spinal Cord Injury II)TUG (Timed Up and Go Test)10-m timed walk6-min walk testUrological functionHand motor functionPlantar reflexIndependence in everyday life of patients is assessed with the Spinal Cord Independence Measure (SCIM II)The number of study-related adverse events (AEs) are measured according to NCI CTCAE, version 5.0

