### Study procedures

First, eligibility for study participation will be assessed and informed consent will be obtained in a pre-screening. Additionally, a pregnancy test will be performed in women with childbearing potential prior to the study intervention. After that, eligible patients undergo a baseline examination comprising a short medical history, a neurological examination (AIS/ISNCSCI), radiological imaging, assessment of the presence of pathological reflexes (priapism, plantar reflex), and documentation of pre-operative interventions.

ESWT is applied peri-operatively under general anesthesia (ideally post-operative immediately after skin closure) or within the first 48 h after trauma.

After the study intervention, surgical interventions and intra-operative diagnosis shall be documented. Also, findings from post-operative imaging and the time sequence of the acute care chain are recorded.

The first follow-up exam should be performed as early as 24–72 h after surgery consisting of a comprehensive medical history and drug anamnesis, an assessment of pre-existing neurological deficits, a neurological examination (AIS/ISNCSCI and plantar reflex), a gait analysis, assessment of urological function, rating of injury severity (Injury Severity Score (ISS)), survey of comorbidities (Charlson Comorbidity Index (CCI)), and questionnaires addressing activities of daily life (Spinal Cord Independence Measure (SCIM) and the Walking Index for Spinal Cord Injury II (WISCI II)). Also, a patient diary is handed out to every patient during the first study visit in which patients should record spasms (Penn Spasm Frequency Scale), medication (drug name and dosage), and any important subjective or objective changes in the neurological symptoms.

The 2nd (day 14–21), 3rd (3 months), and 4th (6 months) follow-up visits consist of a neurological examination, a gait analysis, assessment of urological function, and questionnaires addressing activities of daily life. Parameters from routine blood chemistry and changes in medication shall be documented at each study visit. At the last follow-up exam (6 months), the stability of osteosynthesis is re-evaluated according to X-ray/CT, and a copy of the patient diary is filed at the study site.

The study procedures are depicted in a flowchart, as well as in tabular format in the supplementary material.

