##### Secondary (exploratory) endpoints and control variables

Depending on the scales, the secondary endpoints will be reported descriptively as means with standard deviations, medians, and frequencies. If tests will be conducted, then an alpha less than 0.05 is considered as significant. All these tests are exploratory to get additional ideas on the impact of the treatment.

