### Handling of missing, unused, or faulty data; drop-outs; and terminations

In order to counteract missing values as best as possible, the study will be carried out according to the GCP principle (Good Clinical Practice). Additionally, a regular evaluation of the collected data will take place. If missing values are detected, an attempt will be made to subsequently determine them and/or to document the reasons.

Missing values concerning the primary endpoint are estimated according to the Last Observation Carry Forward principle (LOCF). If possible, the same procedure is used for the secondary endpoints. In all other cases, an analysis of the observed data will be carried out.

The systematically documented reasons for drop-outs will be evaluated to see if they can be used as a predictor for the endpoints and thereby additional insights into the therapy can be gained.

A sensitivity analysis will be performed in order to estimate the effect of missing data and outliers on the study endpoints.

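### The timed walking tests are taken only in patients who regain walking, so the exploratory between-arm comparison is made within subsets chosen by a post-randomisation outcome and can be attenuated or, under some assumptions, reversed

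*Protocol article*

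**What the plan says.** All references are to the protocol article.

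- **Objective.** The Secondary objective section covers "the ability to walk, urological function, quality of life, and independence in everyday life over time and in comparison between the groups".
- **Endpoints.** Walking ability is represented by WISCI II, TUG, the 10-m timed walk and the 6-min walk test, listed under "Secondary (exploratory) endpoints and control variables". The proportion of patients able to walk is not listed as an endpoint.
- **Who is measured.** The Gait analysis section says that these four measures are "assessed in patients who regain walking ability with or without auxiliaries".
- **Visits.** Study procedures says that the second to fourth "follow-up visits consist of a neurological examination, a gait analysis, assessment of urological function, and questionnaires addressing activities of daily life". At the first follow-up it names WISCI II among the questionnaires, separately from the gait analysis and with no restriction to walkers.
- **Analysis.** Depending on scale, "the secondary endpoints will be reported descriptively as means with standard deviations, medians, and frequencies". Testing is optional: "If tests will be conducted, then an alpha less than 0.05 is considered as significant".
- **Missing data.** LOCF is the rule for the primary endpoint. "If possible, the same procedure is used for the secondary endpoints"; otherwise the observed data are analysed.
- **Analysis set.** Calculation of the composite endpoint and Definition of collective analysis both commit to intention-to-treat.

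**The concern.** Whether a patient regains walking is settled after randomisation and is one of the things the treatment is meant to change. Patients with AIS A to D lesions are eligible, so a sizeable non-walking group is to be expected. If the tests are summarised only in those who produced a value, the two sets of walkers need not be comparable. An effective treatment may bring weaker patients over the threshold into walking. They enter the treated arm's average, while their counterparts in the control arm are left out.

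The missing-data rule does not repair this. A patient who never walks has no earlier timed value to carry forward and so falls to the observed-data rule and out of the summary. The intention-to-treat commitment is then not met for these tests.

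At stake is the reading of one secondary objective. A result pointing the wrong way, perhaps with a p-value below 0.05, would mislead even as exploratory evidence.

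**Working it through.** **The plan's own figures.** The article gives none for walking. Its primary design (41, 82 and 123 per arm; one-sided 5%; 80% power; p = 0.6) reproduces by simulation with the stated bounds: type I error 0.0497 and power 0.807. That design is not in question. It supplies the arm sizes and target effect used below.

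**Assumed inputs (not in the article).** 6-min walk; 30% of controls walk, mean 300 m; treatment adds a fraction e of new walkers, mean 120 m; patients who would walk anyway gain g metres; no patient is harmed.

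**Step 1: arithmetic with e = 0.10, g = 0.**
- Walkers only, treated: (0.30 × 300 + 0.10 × 120) / 0.40 = 102 / 0.40 = 255 m. Control: 300 m. Difference -45 m.
- All patients, non-walkers at 0 m: treated 102 m, control 0.30 × 300 = 90 m. Difference +12 m.

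**Step 2: range.** The walkers-only difference reaches zero when g = e × (300 - 120) / (control walking rate).

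| Control walking | e | Walkers-only difference at g = 0 | Break-even g |
|---|---|---|---|
| 30% | 5% | -26 m | 30 m |
| 30% | 10% | -45 m | 60 m |
| 30% | 15% | -60 m | 90 m |
| 50% | 10% | -30 m | 36 m |

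Above break-even the sign is right. With 50% walking, e = 10% and g = 40 m, the walkers-only difference is +3 m, against 182 - 150 = +32 m over all patients.

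**Step 3: sampling.** 4,000 simulated trials per case, 30% versus 40% walking, SD 100 m for existing and 60 m for new walkers (also assumed).

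| Per arm | g | Walkers-only mean favours control | Same, with two-sided p < 0.05 |
|---|---|---|---|
| 123 | 0 m | 97% | 45% |
| 123 | 20 m | 89% | 21% |
| 41 | 0 m | 85% | 17% |
| 41 | 20 m | 75% | 9% |

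**Step 4: rank comparison over all patients, non-walkers tied worst, g = 0.** The probability that a treated patient does better, counting ties as half, is made up of:
- both unable: 0.5 × 0.60 × 0.70 = 0.210
- only the treated patient walks: 0.40 × 0.70 = 0.280
- both walk, treated is an existing walker: 0.5 × 0.30 × 0.30 = 0.045
- both walk, treated is a new walker: about 0.002

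The sum is 0.537, in agreement with the simulated 0.54, and lies on the correct side of 0.5.

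**Step 5: a case without reversal.** Suppose every patient's latent walking capacity shifts by the plan's target effect, √2 × z(0.6) = 0.358 SD, and 30% of controls walk. Then 43.4% of treated patients walk, and the walkers' means above the threshold are 0.635 and 0.740 SD. The walkers-only difference is 0.105 SD: right sign, but well below the 0.358 SD that each existing walker gained. For control walking rates of 20% to 50% it is 0.087 to 0.145 SD.

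**The case against.** The strongest reply is that the Gait analysis section is a measurement rule. Timed walking tests cannot be done by someone who does not walk, no sentence declares a walkers-only analysis population, and the scoring of inability is commonly left to an analysis plan that is not shown. The word frequencies in the analysis section also leaves room for a proportion walking. In part this stands: a reader might infer that the plan announces a walkers-only comparison, and it does not. But the collection rule is stated, the fallback to observed data is stated, and neither the intention-to-treat statements nor the mention of frequencies gives a non-walker a result. An analysis plan can change the summary; it cannot reliably recover a status that sites were not asked to record.

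Three further objections stand and limit the point.

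- **WISCI II.** A reader might count it as walkers-only throughout, or as unrestricted at every visit. The article supports neither. It names WISCI II without restriction at the first follow-up only and lists it under the restriction in Gait analysis. The two sections need reconciling.
- **Non-walkers as a known worst result.** This is tempting but not always true. Hypothesis formulation and testing procedure notes that limb injuries often accompany spinal trauma, so inability to walk, especially at early visits, may not come from the cord.
- **Reversal.** It depends on chosen inputs: slow new walkers and little gain in those who would walk anyway. Step 5 shows that a uniform benefit only attenuates the difference.

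**Conclusion.** The point holds in limited form. For TUG, the 10-m walk and the 6-min walk, following the article as written compares the arms within subsets selected by a post-randomisation outcome, which does not answer the stated between-group objective. For WISCI II the finding is an inconsistency between Gait analysis and Study procedures.

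Under the assumed inputs the walkers-only difference in 6-min distance runs from -60 m to slightly positive while the all-patient difference always favours treatment; under a uniform shift it keeps its sign at 0.105 SD against 0.358 SD. All walking rates, distances and SDs are assumptions.

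Two stronger readings are not supported. One is that an effective treatment will look worse: it can, but need not. The other is that the trial's main conclusion is at risk: these endpoints are exploratory, and the primary delta.TMSC test, its error rate and its sample size are untouched. It is also not established that a 3-month walking time would be carried forward for a patient who can no longer walk at 6 months, since the article does not say whether inability counts as missing. The change is worth making but is not critical.

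**What to change.** 1. Reconcile Gait analysis with Study procedures so that WISCI II is scored in every patient assessed.
2. Record at each visit whether the patient can walk and, if not, why: neurological, limb injury or other.
3. Report the proportion able to walk per arm among all randomised patients, with the number of unknown status shown.
4. At 6 months compare the timed tests by ranks or medians. Give patients unable to walk for neurological reasons the worst rank (for TUG and 10-m time, beyond the longest observed time). Vary the rank of those unable for other reasons in a sensitivity analysis, and handle non-attenders as missing.
5. Keep walkers-only means as supplementary description, labelled as not a randomised comparison.

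**Cost.** One short field per visit and a few sentences of analysis text; no change to treatment, sample size or the primary analysis. The field should be added while recruitment continues, because status not recorded at a visit may be hard to recover. The statistical price is many ties at the worst rank, so ranks or medians replace means. Where fewer than half of each arm walk, as in the 30% versus 40% illustration, both all-patient medians sit at the worst value, so ranks and the proportion walking would carry the comparison.

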#### Urological function

Urological function will be assessed with a query including questions regarding bladder and bowel function (for a detailed list of questions, please refer to the supplementary material).

#### Hand motor function

An evaluation of hand motor function is assessed in those patients who have their lesions above the level T5 with the Nine-Hole Peg Test (NHPT) [55], if feasible, and the Grasp and Release Test (GRT) [56]. Additionally, several grasp tasks are recorded (see supplementary material).

#### Differentiation: nerve root lesion vs. spinal cord lesion

In order to differentiate between isolated nerve root lesions and spinal cord lesions, or a combination of both, a neurologist will clinically classify the location of the lesion.

#### Charlson Comorbidity Index (CCI)

Comorbidities are quantified with the CCI once during the inpatient stay within the first days. The CCI serves as a possible explanatory variable in statistical analysis.

#### Injury Severity Score (ISS)

The Injury Severity Score (ISS) is recorded once during the inpatient stay (ideally pre-operatively; if this is not possible for reasons of timing, within the first 3 days) and serves as an explanatory variable.

#### Subjective physical activity prior to injury

Physical activity prior to the injury is assessed retrospectively at the second follow-up examination (days 14–21) using a subjective self-administered questionnaire. The level of physical activity is considered an important confounder on rehabilitation. The questionnaire has been compiled exclusively for this use case and this patient population. Different types of sports are listed, and the patients should give an estimation on how often, how long, and at what intensity they used to participate in sports.

#### Imaging

The radiological examination by X-ray and/or CT and/or MRI is carried out as part of standard clinical care and data are used for study-related purposes as well. Spinal fractures are graded according to AO classification of the spine (AO 50-53) [57–59].

If fracture classification is not possible with data from the CT scan, an MRI is recommended and the following items should be assessed: (i) spinal lesion, (ii) bone marrow edema, and (iii) ligamentous lesion. For the evaluation of spinal lesions, the MR classification system based on axial images for cervical compressive myelopathy will be used [60]. Ligamentous lesions will be quantified by assessment of the integrity of the posterior ligament complex [61–63]. Data from the MRI scan should be stored on a CD and sent to the Austrian Spinal Cord Injury Study (ASCIS) office in Salzburg, where a trained neuroradiologist will evaluate the images. This should provide a deeper insight in the prognostic value of fracture morphology.

An MRI is mandatory as early as possible in cases suspicious for complete transactional medulla lesions according to neurological examination. In addition to the standard spinal imaging, a diffusion tensor imaging (DTI) medium resolution sequence with 3 b values is recommended.

### Investigational Medical Device (IMD)

The Medical Device used in this trial is a shockwave generator produced by MTS Medical UG, 78467 Konstanz, Germany. The orthogold100® uses patented MTS Spark Wave® technology.

#### Mode of administration

The extracorporeal shockwave therapy is applied once at the level of the lesion and 5 segments above and below or below the occiput (in lesions higher than C6) and above the sacrum (in lesions lower than T12). The transducer is held in an approximated angle of 45° paravertebral from both sides. In addition, the ESWT is applied to the soles of both feet on the medial side of the plantar surface. In patients who require surgical treatment, the ESWT is applied peri-operatively under extension (about 15 to 20 min) of the general anesthesia (ideally post-operative immediately after skin closure) or within the first 48 h after trauma.

If no surgery is required, the ESWT or placebo application is applied as soon as possible within 48 h from the first recognition of neurological symptoms, both in the intensive care unit after surgery or in the normal ward.

For the application, a sterile film is placed in the treatment area and ultrasound gel is used. The study intervention takes approximately 20 min. In the control group, the same procedure is performed, but without the device emitting extracorporeal shock waves using a dummy head.

The application of the ESWT, as well as placebo ESWT, takes place in a prone position if surgical treatment takes place in a prone position. If the surgery takes place in a supine position, patients are placed in a lateral or prone position post-operatively to apply ESWT.

The treating physician together with the team of medical staff will decide whether an additional 20 min of anesthesia is justifiable for the individual patient. For those who cannot give consent to participate prior to the surgical intervention and are still eligible post-operatively (still within the time frame of 48 h), the medical team has to weigh up if a change of position to prone or lateral position is possible without compromising the individual medical condition.

The follow-up examinations shall be blinded [64]. In order to ensure blinding of the examiner, the entire operating room staff and all persons involved in the application of the study intervention are required to keep the group allocation as a secret.

#### Parameters of the ESWT

ESWT head: focused (OE50)Level of filling of the therapy head: 1 (1-5)Frequency: 5 (3-5) HzEnergy flux density: 0.19 (0.15–0.23) mJ/mm^2^Measurement of the distance between skin surface and spinal cord at the level of the lesion according to CT to determine the pressure during treatment in order to reach the spinal cord sufficientlyNumber of impulses: 5000 at the level of the lesion (2500 pulses bilaterally paravertebral) and 1000 on the medial side of the plantar surface on both feet (500 pulses per foot)Area of treatment: 2500 pulses bilaterally paravertebral and 4 segments above and below (3–5 segments: 3 segments for focal lesions and 5 segments for extensive lesions)

#### Placebo, comparator

For patients randomized into the control group, a dummy applicator will be connected to the shockwave generator.

